4.5 Study Assessments

Interventions, Administration, and Duration

Once the patient has agreed to participate and has signed the consent form, a subject ID number will be assigned. Prior to be enrolled in the study, all subjects will have received the following procedures/tests:

1. History and physical examination.
2. EKG, CBC, electrolytes, creatinine and BUN, PT and PTT.
3. Two intravenous catheters will be started.
4. A non-contrast CT scan of the brain or MRI as per the standard of care at the clinical site.

The subject will then receive open label rt-PA via IV catheter at a dose of 0.9mg/kg, 10% given as a bolus and the remainder given as a continuous infusion over one hour. The maximum dose is 90mg.

The study subject will be monitored in the ED until the completion of the rt-PA infusion, following the standard protocol for monitoring after rt-PA administration for acute stroke within 4.5 hours of onset. Once the infusion is completed, the subject will be transferred to the intensive care unit where the observation as per the standard care protocol will be followed. Blood pressure and neurological status will be closely monitored as per protocol. Observation in the intensive care unit will be for a minimum of 24 hours. Subjects will be under the care of the admitting physician that may also be the study investigator.

A non-contrast head CT will be done between 20-30 hours after administration of rt-PA and at any time before or after if there is the clinical suspicion of hemorrhagic transformation or a decline in the subject’s neurological status. If this is the case, the investigator will be notified and after evaluation of the CT scan and the neurological examination and NIHSS, a primary outcome point will be adjudicated.

The subject will receive standard care for stroke and will be discharged from the hospital, when medically stable, to the appropriate rehabilitation setting. All patients will return for a follow up visit at 90 days and will receive a modified Rankin score, NIHSS and Barthel index.

The subject’s involvement with this study will end at 90 days after the assessment.

Schedule of Evaluations

| Evaluation | Screening  (Day 1) | Entry  (Day1) | 24 hrs | 36  hrs | 90 days |
| --- | --- | --- | --- | --- | --- |
| Informed Consent |  | X |  |  |  |
| Documentation of Disease/Disorder | X |  |  |  |  |
| Medical/Treatment History | X |  |  |  |  |
| Adverse Event Ascertainment |  | X | X | X | X |
| Clinical Assessment | X | X | X | X | X |
| Hematology | X |  |  |  |  |
| Chemistry | X |  |  |  |  |
| Non-Contrast Head CT or MRI | X | X | X |  |  |
| Pregnancy Testing | X |  |  |  |  |
| Questionnaires |  |  |  |  | X |

4.5.1 Screening and Pre-treatment Assessments

These evaluations occur prior to the subject receiving any study interventions.

Screening

Patients will be screened for the study upon arrival to the ED. The stroke team should be alerted and arrive at the bedside within 15 minutes of the patient’s arrival and the investigator will be alerted. If the patient is a candidate for the study, the investigator will invite the patient to participate in the study as soon as possible keeping in mind the need to give the study medication within four and half hours of waking up with symptoms. The patient will receive the standard ED evaluation for acute stroke including:

1. History and physical examination.
2. EKG, CBC, electrolytes, creatinine and BUN, PT and PTT.
3. Two intravenous catheters will be started.
4. A non-contrast CT scan of the brain or MRI per standard of care at the clinical site.

Entry/Baseline

The subject will be consented within 4.5 hours of waking up with stroke. After consent is signed, study drug will be administered.

Informed Consent

Patient or LAR will be approached in a calm and private setting, as much as possible. The investigator will describe the study. The consent form will be explained, time allowed for reading of the form and a copy will be given after signing. A copy of the consent form will remain in the subject’s medical record and in the study archives.

- - 1. Assessments During Treatment

Standard protocol for IV rtPA administration for acute stroke within 4.5 hours will be followed. This includes assessment of neurological status and vital signs every 15 minutes for the first two hours, every 30 minutes for the next two hours and ever hour for the next 16 hours.

Subjects will have a non-contrast head CT between 20-30 hours post rt-PA administration and at any time that there is a clinical deterioration. At 24 hours an NIHSS will be performed and the subject assessed for adverse events and serious adverse events. An NIHSS will be performed if there is a clinical deterioration in addition to the CT scan. Subjects will return for an evaluation 90 days after administration of study drug and will have an NIHSS, Barthel index and modified Rankin score. Theoccurrence of adverse events and serious adverse events will be assessed during all contacts with the subjects.

4.5.3 Follow-Up Assessments

The NIHSS will be used to measure stroke severity at the screening point, at 24 hours after treatment, in the event of clinical deterioration and at 90 days after study drug administration. The Barthel index and modified Rankin score will be administered at 90 days.

- 1. Subject Discontinuation

Subjects have a right to withdraw from the study at any time. Subjects that decide to withdraw from the study within the first 24 hours, will need to have their CT scan at 20-30 hours, and continue observation in the intensive care unit, will not receive antithrombotic therapy during the first 24 hours as per standard of care. No data will be collected on the patient after voluntary withdrawal from the study.

The subject may be withdrawn from the study for any reasons: if it is in the best interest of the subject, intercurrent illness, adverse events, or worsening condition. The IRB, NINDS, Genentech, the OHRP, the FDA, or other government agencies as part of their duties to ensure that research subjects are protected, may request the withdrawal of a subject because of protocol violations, administrative reasons, or any other valid and ethical reasons.

- 1. **Study Discontinuation**

The IRB, NINDS, Genentech, the OHRP, the FDA, or other government agencies as part of their duties to ensure that research subjects are protected, at any time may terminate this study. Reasons for terminating the study may include the following:

- The incidence or severity of adverse events in this or other studies indicates a potential health hazard to subjects
- Subject enrollment is unsatisfactory
- Data recording is inaccurate or incomplete
  1. **STATISTICAL METHODS**

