2.0 OBJECTIVES

The primary objective of this study is to evaluate the safety of intravenous rt-PA in patients waking up with symptoms of acute stroke and presenting to the ED within 4.5 hours from awakening and having either a non-contrast head CT without hemorrhage and without hypodensity more than 1/3 of the MCA territory; or MRI demonstrating no hemorrhage, and with a DWI lesion no greater than 70mL and FLAIR without a well demarcated hyperintense lesion that is more than 1/3 of the MCA territory.

Phase II, safety study.

2.1 primary Endpoints

1. Symptomatic intracerebral hemorrhage (sICH) within 36 hours of treatment. We will collect data on symptomatic intracerebral hemorrhage by using the ECASS 3 criteria as well as the original NINDS IV rt-PA trial criteria for comparison.

- In ECASS 3 symptomatic intracerebral hemorrhage is defined as: Any extravascular blood in the brain or within the cranium associated with a clinical deterioration defined as an increase in 4 points on the NIHSS, or that lead to death and was identified as the predominant cause of neurological deterioration.
- In the original NINDS IV rt-PA trial symptomatic intracerebral hemorrhage is defined as: A hemorrhage not seen in previous CT scans and there was a suspicion of hemorrhage or any deterioration in neurologic status.

2.2 secondary Endpoints

1. Asymptomatic intracerebral hemorrhage occurring at any time during the study.
2. Symptomatic intracerebral hemorrhage by ECASS 3 and the original NINDS IV rt-PA trial criteria occurring at any time during the study.

3. Efficacy measures:

a. Modified Rankin score, NIHSS, Barthel index at 90 days

b. NIHSS at 24hrs

c. Mortality at 90 days.

- 1. STUDY DESIGN
  2. **DESCRIPTION OF THE STUDY**

Design:

The study proposed is a one arm, open label study. The aim is to test the safety of IV rt-PA in stroke upon awakening.

The null hypothesis (Ho) is that IV rt-PA in this population will have a symptomatic intracerebral hemorrhage rate of less than 6%.

The alternative hypothesis (Ha) is that IV rt-PA will have a symptomatic intracerebral hemorrhage rate of more than 10%, which would be unacceptably high.

Treatment Regimen:

IV rt-PA 0.9mg/kg, maximum of 90mg. Administered by the standard protocol: 10% of the dose by Intravenous bolus injection, followed by infusion of the remainder over 1 hour.

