Treatment will be initiated within 4.5 hours of awakening, with a preferred target door to needle time of 60 minutes or less from arrival to the ED (i.e. the 60 minute door to needle time is a goal but not required for enrollment since the national target for standard IV rt-PA door to needle time is less than 60 minutes in 50% of patients treated).

No antithrombotic medications in the first 24 hours. After that period, choice of antithrombotic medication will be at the discretion of the treating physician

Study Interventions:

Once the patient has agreed to participate and has signed the consent form, a subject ID number will be assigned. Prior to be enrolled in the study, all subjects will have received the following procedures/tests:

1. History and physical examination.
2. EKG, CBC, electrolytes, creatinine and BUN, PT and PTT.
3. Two intravenous catheters will be started.
4. A non-contrast CT scan of the brain or MRI of the brain per the standard of care protocol at the clinical site.

The subject will then receive open label rt-PA via IV catheter at a dose of 0.9mg/kg, 10% given as a bolus and the remainder given as a continuous infusion over one hour. The maximum dose is 90mg.

The study subject will be monitored in the ED until the completion of the rt-PA infusion, following the standard protocol for monitoring after rt-PA administration for acute stroke within 4.5 hours of onset. Once the infusion is completed, the subject will be transferred to the intensive care unit where the observation as per the standard clinical care protocol will be followed. Blood pressure and neurological status will be closely monitored as per protocol. Observation in the intensive care unit will be for a minimum of 24 hours. Subjects will be under the care of the admitting physician that may also be the study investigator.

A non-contrast head CT will be done between 20-30 hours after administration of rt-PA and at any time before or after if there is the clinical suspicion of hemorrhagic transformation or a decline in the subject’s neurological status. If this is the case, the investigator will be notified and after evaluation of the CT scan and the neurological examination and NIHSS, a primary outcome point will be adjudicated. We will use the symptomatic intracerebral hemorrhage definition from both ECASS 3 as well as the original NINDS IV rt-PA trial criteria for comparison.

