3.3.1 Primary Outcome Measure

This is a safety study; therefore the primary outcome is a safety outcome:

- Symptomatic intracerebral hemorrhage rate within 36 hours of treatment. By ECASS 3 and NINDS rt-PA study as stated above.

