5.3 Procedures for Eliciting, Recording, and Reporting Adverse Events

5.3.1 Eliciting Adverse Events

All patients enrolled will have a non-contrast head CT within 20-30 hours post treatment with ACTIVASE or if there is any change or deterioration in neurological status. Presence of hemorrhagic transformation in the CT will be classified as symptomatic if there is a concomitant deterioration in the patient’s neurologic status and as asymptomatic if there isn’t any change.

During the 24-hour, 36 hour and 90 days visit, adverse events will be elicited by asking for new symptoms, diagnosis, changes in health, since the last visit.

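### No NIHSS is scheduled between 24 hours and 90 days, so in the last 12 hours of the 36-hour primary window a non-fatal ECASS 3 event is scored only if someone first notices a decline

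*Protocol*

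**What the plan says.** **Endpoint.** Protocol 3.3.1 names the primary outcome as "Symptomatic intracerebral hemorrhage rate within 36 hours of treatment", by both the ECASS 3 and the NINDS definitions. Section 2.1 gives the two definitions. ECASS 3 requires blood with "clinical deterioration defined as an increase in 4 points on the NIHSS, or that lead to death". NINDS requires a new hemorrhage where "there was a suspicion of hemorrhage or any deterioration in neurologic status". Under Safety Analysis in 4.8, the DSMB analyses the rate by ECASS 3.

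**NIHSS times.** Section 4.5.3 lists the occasions for the NIHSS: "stroke severity at the screening point, at 24 hours after treatment, in the event of clinical deterioration and at 90 days". The text on assessments during treatment agrees: a score at 24 hours, one at 90 days, and one together with a CT at any clinical deterioration.

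**Routine CT.** One non-contrast head CT is done 20 to 30 hours after treatment, with further CT on clinical suspicion or decline.

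**The 36-hour contact.** The schedule of evaluations and Appendix A mark a Clinical Assessment and adverse event ascertainment at 36 hours, without imaging. Neither says what the Clinical Assessment contains. Section 5.3.1 adds: "During the 24-hour, 36 hour and 90 days visit, adverse events will be elicited", by asking about new symptoms, diagnoses and changes in health.

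**Monitoring.** The listed checks of neurological status and vital signs are "every 15 minutes for the first two hours, every 30 minutes for the next two hours and ever hour for the next 16 hours". The study description in section 3, and again 4.5, states: "Observation in the intensive care unit will be for a minimum of 24 hours".

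**The concern.** The score that defines a non-fatal ECASS 3 event has its last scheduled early reading 12 hours before the primary window closes. After that, an NIHSS is taken only once somebody has recognised a decline.

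Several things change at about 24 hours: the last scheduled early NIHSS is done, the minimum intensive care stay expires, and antithrombotic treatment becomes permissible. Section 3.4 says bleeding is most likely within 24 hours but calls it unlikely only after 72 hours, so hours 24 to 36 cannot be treated as free of events.

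The routine CT can also come after the 24-hour score. Section 5.3.1 classes hemorrhage on CT as symptomatic or asymptomatic according to whether neurological status has worsened at the same time. If blood is seen on such a CT and a decline has gone unnoticed, no later scheduled score would correct the classification. The event would move from the primary endpoint to a secondary one.

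The error runs one way, toward a lower sICH count in a study whose purpose is to judge safety. It cannot be repaired in the analysis, because the next scheduled NIHSS is at 90 days.

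**Working it through.** The protocol states no figure for this point, so there is none to reproduce. The check sets its time points side by side.

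**Inputs**
- Primary window: 36 h (2.1, 3.3.1, 4.8.4)
- Last scheduled early NIHSS: 24 h (4.5.3)
- Routine CT: 20 to 30 h (study description in section 3, and 4.5)
- Sample size: 20; hypotheses: sICH below 6% and above 10%; stopping at two events among subjects 1 to 10 and three events among subjects 11 to 20 (4.8)
- Listed checks: 2 h, 2 h and 16 h (assessments during treatment)
- Intensive care observation: at least 24 h (study description in section 3, and 4.5)

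**Step 1. Part of the window after the last scheduled NIHSS**
36 − 24 = 12 h, and 12/36 = 33% of the window. This is a share of time, not of risk.

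**Step 2. Routine CT against the 24-hour NIHSS**
- A CT at 20 to 24 h is followed by the scheduled 24-hour score.
- A CT at 24 to 30 h comes after that score, by up to 30 − 24 = 6 h. No later scheduled score falls inside the window.
- The window remaining after the routine CT is 36 − 30 = 6 h to 36 − 20 = 16 h, with only event-driven imaging.

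**Step 3. Weight of one misclassified event**
- 1/20 = 5 percentage points.
- The two hypothesised rates differ by 10 − 6 = 4 percentage points.
- The stopping counts are two and three, so one uncounted event can decide whether the rule is met.

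The protocol gives no basis for the probability that a decline goes unrecognised, so no expected number of missed events is offered.

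**Step 4. Listed checks against intensive care observation (separate point)**
- 2 + 2 + 16 = 20 h, made up of 8 + 4 + 16 = 28 checks.
- 24 − 20 = 4 h of the minimum intensive care stay have no listed check.

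**The case against.** The strongest reply is that ascertainment is event-driven by design. Any suspicion of hemorrhage or neurological decline requires a CT, notice to the investigator, and adjudication from the CT, the examination and the NIHSS. A non-fatal ECASS 3 event involves a fall of 4 points, which is unlikely to go unseen in a hospitalised patient. The 24-hour NIHSS is listed as a secondary efficacy measure rather than as the instrument for the primary endpoint. This reply stands as far as it goes: a recognised decline at hour 30 would be scored and imaged. It does not cover a decline that nobody recognises, and that is the whole of the point.

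Three stronger readings are tempting, and the documents do not support them.

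- **The endpoint as a whole needs a 4-point change.** It does not. ECASS 3 also counts hemorrhage leading to death, and the NINDS definition has no point threshold. The gap matters most for the non-fatal part of the ECASS 3 rate, although non-fatal cases under NINDS still depend on someone suspecting hemorrhage or noticing deterioration.
- **The 36-hour visit has no NIHSS.** The text does not show this. The schedule has no NIHSS row, so the scores required at screening and 24 hours probably sit under Clinical Assessment, a row also marked at 36 hours. An NIHSS at 36 hours may therefore be intended. But 4.5.3 lists the NIHSS occasions explicitly and omits 36 hours, so a site following that section would not take one.
- **Neurological assessment stops at hour 20.** The listed checks are introduced as part of a standard protocol and need not be exhaustive. A 24-hour NIHSS, at least 24 hours of intensive care observation and the 36-hour assessment follow or overlap. The 20-hour total is a mismatch of wording and does not measure how much of the endpoint window is unobserved.

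It is also fair to say that check frequency and length of intensive care stay are different quantities, which is why that mismatch is treated as minor.

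**Conclusion.** The point holds in a limited form. No NIHSS is scheduled in the last 12 of 36 hours of the primary window, or after a routine CT done later than the 24-hour score. In both situations, scoring a non-fatal ECASS 3 event depends on deterioration being noticed first. Any resulting error lowers the sICH count. Its frequency is unknown and may be small; each such event is worth 5 percentage points with 20 subjects.

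The conclusion assumes that the NIHSS list in 4.5.3 is complete. If the 36-hour Clinical Assessment was always meant to include an NIHSS, the defect is one of wording, and the same edit settles it. This is more than a detail left to an analysis plan, because the protocol itself fixes the collection times and a score that was not collected cannot be recovered.

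The difference between 20 and 24 hours is a separate, minor inconsistency. The documents do not show which passage is intended.

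**What to change.** State in 4.5.3, in the schedule of evaluations and in Appendix A that the existing 36-hour Clinical Assessment includes an NIHSS. State also how adjudication uses it:

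- It is in addition to the deterioration-triggered NIHSS and CT, and does not replace them.
- The 24-hour score and any event-driven scores are considered too. Comparing only the 36-hour score with baseline would miss a subject who improves and then declines, or who declines and then partly recovers.
- A decline found at 36 hours counts as clinical deterioration, so the CT provision already in the protocol applies. An NIHSS alone cannot establish hemorrhage.

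The cost is a few minutes of bedside examination per subject at a contact already scheduled, plus the wording changes.

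Separately, reconcile the 20-hour total of the listed checks with the 24-hour minimum of intensive care observation. Which of them should change is for the sponsor and investigators to decide.

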4.8.1 Analysis of the Conduct of the Study

The study proposed has a single arm, open label study to test the safety of IV tPA in stroke upon awakening. The null hypothesis (Ho) is that IV rt-PA in this population will have a symptomatic intracerebral hemorrhage rate of less than 6%.

The alternative hypothesis (Ha) is that IV rt-PA will have a symptomatic intracerebral hemorrhage rate of more than 10%, which would be unacceptably high.

This is a proof of concept study. We will obtain the frequency of the primary outcome (symptomatic intracerebral hemorrhage within the first 36 hours).

- - 1. Baseline Demographics

The sample size will be 20 patients, to assess the safety of rt-PA in this population. The number of patients with acute stroke treated at Johns Hopkins Hospital (JHH) and Johns Hopkins Bayview Medical Center (JHBMC) from February 1, 2008 to January 31, 2009 was 175 and 196 respectively. Assuming that 12% may present with stroke symptoms upon awakening and be eligible by CT criteria (Based on a retrospective evaluation of one year of stroke patients at JHH), with a rate of agreement to participate of 60%; this would yield 12 and 14 study subjects per year at JHH and JHBMC respectively. Based on this assessment, this study can be completed in one year.

- - 1. Safety Analysis

Because this study is designed to assess safety, the safety analysis is the same as the primary outcome analysis, which is the assessment of the rate of symptomatic intracerebral hemorrhage after IV rt-PA in patients that present to the ED within 4.5 hours of waking up with stroke. A DSMB (composed of one member independent of the investigator team) will conduct an analysis of the rate of symptomatic intracerebral hemorrhage by ECASS 3 criteria.

Symptomatic intracerebral hemorrhages (events) will be evaluated after each subject completes therapy. During the phase of the study in which there are 1-10 subjects enrolled, the study will stop at any point there are two events. During the phase of the study in which there are 11-20 subjects enrolled, the study will stop at any point if there are three events.

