5.2.1 Adverse Event Reporting Period

The study period during which all AEs and SAEs must be reported begins after informed consent is obtained and initiation of study treatment and ends 90 days following the last administration of study treatment or study discontinuation/termination, whichever is earlier. After this period, investigators should only report SAEs that are attributed to prior study treatment.

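### The ban on data after voluntary withdrawal can keep a post-withdrawal sICH out of the 36-hour primary count and the stopping rule

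*Protocol*

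**What the plan says.** The endpoint (Protocol, 2.1 and 3.3.1) is "Symptomatic intracerebral hemorrhage (sICH) within 36 hours of treatment". Treatment is a bolus followed by a one-hour infusion.

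Subject Discontinuation (4.6 in the contents list) describes two routes out of the study:

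- **Voluntary withdrawal.** "Subjects that decide to withdraw from the study within the first 24 hours, will need to have their CT scan at 20-30 hours", and intensive-care observation goes on. The paragraph then closes with "No data will be collected on the patient after voluntary withdrawal from the study".
- **Withdrawal by others.** A separate paragraph lists reasons that include "intercurrent illness, adverse events, or worsening condition". It says nothing about whether data collection continues.

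The stopping rule is in Safety Analysis (4.8.3): "Symptomatic intracerebral hemorrhages (events) will be evaluated after each subject completes therapy". While 1 to 10 subjects are enrolled, "the study will stop at any point there are two events". From 11 to 20 subjects the limit is three. The section does not say how a treated subject who has withdrawn is counted.

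Two other places bear on reporting after a subject leaves. Section 5.2.1 says the adverse event period "ends 90 days following the last administration of study treatment or study discontinuation/termination, whichever is earlier", and after it keeps reporting of serious adverse events (SAEs) attributed to study treatment. Section 5.3.2, item f, asks for expedited reporting of any SAE in a subject who has discontinued, if it is attributed to alteplase.

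**The concern.** In a trial of a single short infusion, leaving the study an hour or a day later does not reduce exposure or the risk being measured. It only removes information. The protocol foresees withdrawal inside the 36-hour window and keeps the scan that would show a bleed, but rules out collecting the result. Read literally, the chart would hold the primary outcome of a treated subject while the study database would not.

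An analysis plan cannot repair this later, because it cannot use data that the protocol says not to collect. Losing a subject who bled can only lower the observed sICH rate and the number of events set against the stopping limits. For a safety trial that is the unsafe direction. With limits of two and three events, one uncounted bleed can decide whether the study stops.

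**Working it through.** **Which events are exposed.** A bleed documented before withdrawal, including one that prompts it, is not removed by the rule. The exposed events are those that occur or are found after voluntary withdrawal and before hour 36.

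**Weight of one event in the final rate.** Inputs from 4.8: 20 subjects, with hypotheses at less than 6% and more than 10%.

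- 1/20 = 5 percentage points; the gap between the two marks is 10 − 6 = 4 points.
- All events seen: 2/20 = 10.0% (exact 95% CI 1.2% to 31.7%).
- One event unseen, subject kept in the denominator: 1/20 = 5.0% (0.1% to 24.9%).
- One event unseen, subject dropped from the denominator: 1/19 = 5.3% (0.1% to 26.0%). The protocol does not state this denominator; it is an assumption.

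**Effect on the stopping rule.** The protocol gives neither a withdrawal rate nor the rule's stopping probabilities, so there is no stated figure to reproduce. I took the rule as two events among the first 10 subjects, or three in total by any later subject, checked after each one. Let P(k) be the binomial probability of k events in 10 subjects at the observed rate. Then

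P(stop) = P(≥2) + P(0) × P(≥3) + P(1) × P(≥2),

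where the first term covers subjects 1-10, and the other two cover subjects 11-20 after zero or one earlier event.

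At 10% with every event seen: P(0) = 0.3487, P(1) = 0.3874, P(≥2) = 0.2639, P(≥3) = 0.0702. P(stop) = 0.2639 + 0.3487 × 0.0702 + 0.3874 × 0.2639 = 0.2639 + 0.0245 + 0.1022 = 0.3906.

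If a share m of events goes unseen, independently of one another, the observed rate is p × (1 − m). At p = 10% this is 9%, 8% and 5% for m = 10%, 20% and 50%. The same formula gives:

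| True sICH rate | All seen | 10% unseen | 20% unseen | 50% unseen |
|---|---|---|---|---|
| 6% | 16.8% | 13.9% | 11.1% | 4.4% |
| 10% | 39.1% | 33.3% | 27.6% | 12.0% |
| 20% | 82.6% | 76.6% | 69.2% | 39.1% |

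The unseen shares are assumptions chosen to show a range.

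**The sections side by side.** Subject Discontinuation allows no data after voluntary withdrawal. Sections 5.2.1 and 5.3.2 f require some: SAEs attributed to the drug. Both cannot hold as written. The SAE route also depends on attribution, and neither section says that such a report enters the primary sICH count or the stopping rule.

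**The case against.** The strongest reply is that a safety net exists. Item f of 5.3.2 keeps SAE reporting open after a subject discontinues. Section 5.2.2 treats an event that fits alteplase's known pattern as related, and 3.4 names intracranial bleeding among the drug's well-described complications. A post-withdrawal sICH would very likely be attributed and reported. This stands in part: loss of the event is possible, not certain. But the net contradicts the no-data sentence and leads to safety reporting, not to the endpoint count.

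The window is also short, subjects spend at least 24 hours in intensive care, and nothing suggests that early withdrawal is common. That stands too, and is why the size above is only illustrative. In addition, 4.8 says only that the frequency of the primary outcome will be obtained; it does not state a test of the final estimate against 6%.

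Stopping collection when a subject withdraws can be a matter of consent. The consent pages are not available, so whether they deal with later use of records cannot be judged.

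A reader might infer two stronger things that the text does not support:

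- *That worsening or an adverse event triggers the data ban.* Those reasons sit in a separate paragraph about removal by others, with no data rule attached. For that route the protocol is silent on follow-up; it does not bar it. The silence deserves a sentence, since clinical deterioration is part of both sICH definitions.
- *That 5.2.1 closes adverse event reporting when one subject leaves.* The protocol has separate headings for subject and study discontinuation, and the wording in 5.2.1 more likely means the end of the whole trial.

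**Conclusion.** The concern holds for voluntary withdrawal before hour 36. Followed as written, the no-data sentence can leave an sICH in a fully exposed subject out of both the primary count and the stopping rule, although the scan that would show it is still required. The SAE provisions reduce that risk but conflict with the sentence and are not linked to either count.

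One lost event moves the observed rate by about 5 points. At a true 10% rate, which the protocol calls unacceptable, the chance of stopping falls from 39.1% to between 33.3% and 12.0% for assumed unseen shares of 10% to 50%. The direction follows from the text. The size rests on those assumed shares, on independent loss of events, and on the reading of the rule given above.

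**What to change.** Amend Subject Discontinuation so that withdrawal after rt-PA ends study visits only. For every treated subject, take the following from the medical record unless the subject refuses record use:

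- sICH status to 36 hours under both definitions, including the result of the CT already required;
- SAEs;
- vital status at 90 days.

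State that removal by the investigator or by an oversight body does not end this follow-up. State in 4.8 that all treated subjects count in the primary sICH rate and in the stopping rule. Reconcile the no-data sentence with 5.2.1 and 5.3.2 f, and make clear in 5.2.1 whether discontinuation means the subject or the study.

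The cost is protocol and consent wording plus a chart look-up for each withdrawn subject. Patient care does not change. A subject may still refuse record use; such a subject should be reported as treated with unknown 36-hour status.
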